### Fidelity

Participant fidelity is assessed based on participation in-clinic visits, phone calls, and website use. Fidelity for the research team includes scripts and objective cut-off measures for interacting with participants. There are set cut points for determining when a scheduled participant interaction is counted as missed. For example, if a participant and coach have a phone call scheduled but the participant has not answered by the third call, the coach discontinues calling. If the participant does not respond to the coach’s voicemail within two days then that week’s phone call is counted as missed. Also, the coach has a checklist to follow for each phone call. The project coordinator reviews call logs and clinic visit logs once a month to ensure adherence is correctly documented by the health coach. The project coordinator also randomly selects and reviews 20% of the call checklists. These fidelity protocols increase the project’s overall internal validity and replicability.

### Data analysis

Data analysis is performed by a project coordinator and statistician who are blinded to the intervention group assignment. Participant attrition, session attendance, and instrument completion are recorded and analyzed using descriptive statistics. We hypothesize that by the end of the study, 70% of the participants will be retained, 70% will participate in all coaching sessions, and 100% will have completed at least 80% of the survey instruments at each data collection point. Data will be analyzed with mixed effects models to assess the effect of POWERS_*for*ID_ on participant outcomes. A mixed model is a generalization of the standard linear model that permits repeated measures data to exhibit correlation and non-constant variability over time. We will use each outcome as a time-varying dependent variable and group (POWERS_*for*ID_ vs. control) as main fixed effects. Baseline demographics will be entered as time-invariant covariates if baseline group differences are observed. Intercept will be modeled as random effects. We hypothesize that the trajectory slope of participant outcomes will be more favorable in the POWERS_*for*ID_ group compared to the control group, which will result in a significant GroupXTime interaction effect. We will analyze our data using both on-treatment and intent-to-treat approaches. Participants lost through attrition will be compared on demographic and prognostic variables to those who remain in the study to examine the sample representativeness and potential treatment bias.

Qualitative data analysis from the POWERS_*for*ID_ study results will address motivational interviewing applications, barriers, and successes of the intervention. We will perform thematic analysis using ATLAS.ti software. Thematic analysis is an iterative process that involves the researcher as the instrument for: (1) coding qualitative data; (2) cross-comparing codes for pattern identification; (3) grouping codes into broader themes; and (4) interpreting thematic relationships [31, 40]. We will also report on the level of data saturation achieved.

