### Intervention

The study design is a 24-week RCT to assess the efficacy of POWERS_*for*ID_ on weight loss and overall health status (target sample: n = 70). The primary aim of this study is to test the feasibility and efficacy of the POWERS_*for*ID_ intervention in obese adults with ID. With a moderate effect size of 0.62 and a two-sided alpha of 0.05, a sample size of 35 participants per group will achieve a power of 0.80. After consent, all participants complete baseline measures and are then randomized to one of two conditions: (1) POWERS_*for*ID_ intervention; or (2) control. De-identified patient demographic data were used to conduct simulation checks to ensure balanced group allocation and to determine a proper randomization protocol. Simulation checks accounted for age, race, and ethnicity. After the simulation checks, a simple randomization sequence was developed. Each individual randomization assignment was then sealed in an envelope. Participants have equal probabilities of randomization to the intervention or control group. When it is time to randomize a participant to either arm, the health coach opens the next envelope in the sequence to reveal the group assignment. Participants are recruited, enrolled, and randomized by the health coach; all other research staff have been blinded to randomization. Participants randomized to the control group receive usual care from the clinic and related clinic staff. In addition, during the 24-week intervention, control group participants complete assessments at baseline, and at weeks 6, 12, and 24. Upon completion of the study period, control group participants are provided educational materials from an online information and resource center specializing in health and disability, as well as the option to contact a toll-free number and speak with an information specialist for further advice on physical activity and nutrition.

Participants randomized to the intervention group receive access to the POWERS_*for*ID_ website and review the interface with the health coach. The participant and coach schedule an initial phone call to review strategies to improve physical activity and diet. Subsequent phone calls occur weekly until the 12th week of the intervention and biweekly during weeks 13–24. All participants visit the clinic at baseline and at weeks 6, 12, and 24. The study protocol is summarized in Fig. 2 (based on SPIRIT 2013 guidelines).

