#### Goal setting

After the participant and caregiver (if applicable) complete the baseline HAP, the individualized (automated) goals and objectives are generated by the POWERS_*for*ID_ system and reviewed by the health coach before the first online meeting and phone call with the participant. After the health coach and the participant agree to the physical activity, nutrition and behavioral reinforcement plan, the project coordinator arranges the first coaching call. The initial call lasts approximately 30–60 min and is used to review the goals and implementation strategies selected by the POWERS_*for*ID_ system (established from the baseline HAP) and to set a schedule for the weekly (first 12 weeks) and biweekly (last 12 weeks) coaching calls, which last approximately 20–30 min. The goals and implementation strategies in physical activity and nutrition are finalized with the participant to ensure that they are consistent with the participant’s abilities, interests, and availability of community resources. Discussion points are noted by the health coach, permitting the research staff to review calls and monitor recommendations. During the calls, participants learn new strategies to improve their nutrition and physical activity behaviors (e.g. viewing a video of a certain activity, learning about healthy food choices) and are able to check the website with a password protected ID at any time for updates on their progress. Caregivers also have access to the system to view the progress of their care recipient.

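### The project coordinator is named as a blinded analyst but arranges the first coaching call and audits call records, which are described for the intervention arm only

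*Protocol article*

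**What the plan says.** On blinding, the protocol article makes two statements. The Data analysis section says: "Data analysis is performed by a project coordinator and statistician who are blinded to the intervention group assignment". The Intervention section, in its account of envelopes and enrolment, says: "Participants are recruited, enrolled, and randomized by the health coach; all other research staff have been blinded to randomization".

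On the project coordinator's duties, Goal setting says that once coach and participant have agreed a plan, "the project coordinator arranges the first coaching call". Fidelity adds: "The project coordinator reviews call logs and clinic visit logs once a month to ensure adherence is correctly documented by the health coach". It continues: "The project coordinator also randomly selects and reviews 20% of the call checklists". Goal setting also has the coach's call notes kept for a wider group, "permitting the research staff to review calls and monitor recommendations".

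On who is called, the Abstract and the Intervention section give scheduled coaching calls to the intervention arm only. Controls receive usual care and the clinic assessments. They are offered educational materials and an optional telephone information line only after the study period.

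**The concern.** If coaching calls belong to one arm, anyone who books such a call for a named participant, or reads that participant's call record, knows the arm. The coordinator does both and is also one of the two people who analyse the data.

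Two things are at stake. A report that repeats the article's statement would credit the trial with a safeguard that one of its two analysts does not have. In addition, the Data analysis section leaves some judgement to the analysts. Baseline demographics enter the mixed models only when the groups are seen to differ, and the article gives no criterion for that. The on-treatment analysis also has to be put into practice by someone. Blinding is meant to keep knowledge of the arms out of such judgements.

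**Working it through.** This is a check of consistency between sections. The article gives no figure for it to reproduce.

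1. **Who has coaching calls?** The Abstract and Intervention sections describe them for intervention participants, weekly in weeks 1–12 and every two weeks in weeks 13–24. No scheduled call is described for controls during the 24 weeks. A coaching-call record therefore marks an intervention participant.

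2. **What does the coordinator handle?**
   - *First call (Goal setting).* Arranging a call requires knowing with whom it is arranged, so one call per participant is enough to disclose the arm. Only this first call is assigned to the coordinator. The section on coaching calls and motivational interviewing has calls scheduled in advance with the coach, participant and caregiver.
   - *Call logs (Fidelity).* These are reviewed monthly, with no sampling mentioned.
   - *Call checklists (Fidelity).* A random 20% are read. As a rough scale, assume the planned 35 participants in the intervention arm and every call made. Calls per participant: 12 + 12/2 = 18. Calls in total: 35 × 18 = 630. Checklists read: 0.20 × 630 = 126.
   - *Clinic visit logs (Fidelity).* Both arms attend clinic visits, so these logs alone reveal nothing. Read beside the call logs they give the full roster, and a participant with visits but no calls is probably a control. The inference is not exact. The first call is arranged only after a plan is agreed, so an intervention participant who leaves before then would look like a control.

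3. **What does the article claim about the same role?** Data analysis says the coordinator who analyses the data is blinded to group.

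4. **Comparison.** Steps 1 and 2 give the coordinator the arm of every intervention participant who reaches a first call, and the probable arm of the rest. Step 3 says the coordinator does not know it. Both cannot hold for the same person.

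5. **The statistician.** No section gives the statistician any contact with calls, logs or checklists, so the contradiction stops at the coordinator.

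**The case against.** **Two coordinators, or masked logs.** Data analysis speaks of a project coordinator and the other sections of the project coordinator, so two people are conceivable, as are de-identified logs. The article mentions neither. Masked logs would not help with the first call, which cannot be arranged with an anonymous participant.

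**The Intervention sentence may mean something narrower.** It stands beside the description of sealed envelopes and can fairly be read as keeping the assignments from other staff at randomisation. It need not promise that nobody connected with coaching ever learns an arm. This stands. A reader might infer that the sentence is plainly false, but it is ambiguous and needs clarifying. The firm contradiction is with Data analysis.

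**The discretion is small.** A reader might infer that an unblinded analyst could choose between on-treatment and intent-to-treat. The article does not support that, because it plans both. The covariate rule is limited to baseline demographics and depends on an observed group difference, which is equally visible with arms coded A/B. What remains is the judgement of what counts as a difference and how on-treatment is applied.

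**The main measurements are out of reach.** Under Outcomes, anthropometry is done at clinic visits and lipids come from blood tests. No section gives the coordinator a part in measuring outcomes or assigning arms. This also stands, and it confines the problem to the analysis stage.

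**Conclusion.** The concern holds for the project coordinator: one of the two named analysts learns allocation through duties that the article itself assigns. It would be wrong to infer that both analysts are unblinded, since nothing shown contradicts the statistician's blinding.

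The effect on the estimates cannot be quantified, and the article gives no evidence that a result would change. The case for correction is that the stated safeguard is absent for one analyst and is cheap to restore.

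The conclusion assumes that the coordinator is the same person throughout, that the call records identify participants, and that controls receive no coaching calls. The article describes nothing to the contrary on any of these.

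**What to change.** 1. Have the statistician alone run the between-group analysis, on a locked file with arm coded A/B. The coordinator keeps the call and fidelity duties.
2. Sequence the work. First finalise the covariate decision and the intent-to-treat models. Then release call, website-use and points data for the on-treatment and adherence analyses. Withholding those data until every outcome model is final would not work, because Fidelity bases participant adherence on visits, calls and website use, and an on-treatment analysis would ordinarily need them. Releasing them earlier could disclose the arms to the statistician.
3. Reword Data analysis to say that the statistician is blinded and the project coordinator is not.
4. Clarify in Intervention that "all other research staff have been blinded to randomization" does not cover staff who arrange or review coaching calls.

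The cost is one reassigned task and a few sentences. The statistician is already named, although the article does not say how much of that person's time is available. Trial status reports recruitment as still open, so the change can be made before the final analysis.

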**Methods:**

Obese adults with mild-to-moderate ID (n = 70) are randomized to the POWERS_*for*ID_ intervention or control group for a 24-week trial. Each group undergoes an assessment that includes body weight, waist circumference, and percent body fat at baseline and at weeks 6, 12, and 24. Physical activity barriers, healthy eating barriers, food frequency, and psychosocial wellbeing are measured at baseline and at weeks 12 and 24. Blood lipids are assessed at baseline and 24 weeks. Participants randomized to POWERS_*for*ID_ receive access to the POWERS_*for*ID_ website and calls from a health coach (weekly during weeks 1–12, biweekly during weeks 13–24). The health coach employs motivational interviewing techniques adapted for individuals with ID to promote behavior change. Participants randomized to the control group receive standard clinical weight-loss care. Differences in weight, waist circumference, blood lipids, percent body fat, and psychosocial self-report will be assessed. Barriers and facilitators of implementation as well as perception of study outcomes will be conducted via qualitative analysis.

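### The visible text names no primary efficacy outcome, time point or analysis set, and the effect size 0.62 and alpha 0.05 are tied to none of the outcomes tested

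*Protocol article*

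**What the plan says.** - **Aim.** The Intervention section gives the primary aim as feasibility and efficacy, with efficacy directed at weight loss together with overall health status. The second of these is not defined as a variable.
- **Sample size.** The same section bases its calculation on these inputs: "With a moderate effect size of 0.62 and a two-sided alpha of 0.05". From them it claims 0.80 power with 35 people in each arm. It gives no outcome, visit, mean difference, standard deviation or test for these figures.
- **Outcomes.** The abstract lists five without rank: "Differences in weight, waist circumference, blood lipids, percent body fat, and psychosocial self-report will be assessed". Table 2 and the HAP questionnaires section list many more, also unranked. Weight is measured at baseline and weeks 6, 12 and 24, and no visit is singled out.
- **Analysis.** The Data analysis section states: "We will use each outcome as a time-varying dependent variable". It hypothesises a more favourable slope for participant outcomes in general, shown by a significant group-by-time interaction. Both intent-to-treat and on-treatment analyses are planned, and neither is said to decide.

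**The concern.** A power statement with one alpha implies one deciding test. The analysis section instead describes a set of equal tests. A reader cannot tell which result would make the trial positive, or which test the stated 5% error rate and 0.80 power describe. Because overall health status is undefined, almost any scale in Table 2 could be presented as meeting the aim. The Discussion says that a demonstration of efficacy could lead to use in similar clinics, so the claim has consequences.

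**Working it through.** **1. The plan's own figure.** Inputs from the Intervention section: effect size d = 0.62, two-sided alpha 0.05, 35 per group, equal allocation, power 0.80.

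- Normal approximation: power = Φ(d·√(n/2) − 1.96) = Φ(0.62 × √17.5 − 1.96) = Φ(2.594 − 1.960) = Φ(0.634) = 0.737.
- Two-sample t-test (noncentral t): power = 0.725.
- Number per group for 0.80: 2 × (1.960 + 0.842)² / 0.62² = 40.8, so 41 (42 with the t-test).
- A one-sided 0.05 test would need 33 per group, but the plan says two-sided. At 35 per group and two-sided 0.05, 0.80 corresponds to d of about 0.67–0.68.

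The stated 0.80 is therefore not reproduced for a simple two-group comparison. With no outcome or test named, it cannot be checked against any other model.

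**2. Number of outcomes.**

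- Narrow count, from the abstract: weight, waist, lipids, percent body fat and psychosocial self-report = 5.
- Wide count, from Outcomes, Table 2 and HAP questionnaires: weight, waist and percent fat (3), lipids counted once and blood sugar (2), the ten HAP questionnaires (10), dietary barriers (1) = 16. Pedometer steps and daily points are left out because they come from materials and logging described for the intervention group. Splitting lipids or questionnaires into components would raise the count.

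**3. Chance of at least one p<0.05 with no true effect.** Take one interaction test per outcome at two-sided 0.05.

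- Independent tests: 1 − 0.95^k. For k = 5: 1 − 0.7738 = 0.226. For k = 16: 1 − 0.4401 = 0.560.
- Common correlation ρ between the test statistics: 1 − ∫ [Φ((1.96 − √ρ·u)/√(1−ρ)) − Φ((−1.96 − √ρ·u)/√(1−ρ))]^k φ(u) du.

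| Outcomes | ρ = 0 | ρ = 0.3 | ρ = 0.5 | ρ = 0.7 |
|---|---|---|---|---|
| 5 | 0.23 | 0.21 | 0.18 | 0.15 |
| 16 | 0.56 | 0.48 | 0.37 | 0.26 |

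A simulation of 200,000 runs gave 0.376 for 16 outcomes at ρ = 0.5, in agreement. Counting only false positives that favour the intervention, the values at ρ = 0 and 0.5 are 0.12 and 0.09 for five outcomes, and 0.33 and 0.19 for sixteen.

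The correlations are assumptions; the article gives none. Running two analysis sets adds somewhat to each figure, by an amount not computed here.

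**4. After naming one primary test.** The error rate for the efficacy claim is 0.05. If all 16 outcomes stayed equal under a Bonferroni rule (0.05/16 = 0.003125), power per outcome at 35 per group would be about 0.33 (t-test). A single primary test is clearly the better course at this sample size.

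**The case against.** - **No any-scale-wins rule is written.** A reader might infer that a significant result on any one scale will be declared efficacy. The article does not say so; its hypothesis concerns the outcomes collectively. This stands. The percentages show what the wording permits, not a decision rule that the plan states.
- **Weight is plainly the main interest.** It leads the abstract and the objectives, and it appears in the same section as the sample size. This stands in part. Weight is never designated, it is paired with overall health status, and the visit, contrast and analysis set would remain open even if weight were assumed. Equally, a reader should not infer that the alpha belongs to no test at all: the text leaves it unassigned.
- **Unseen material may settle the matter.** Multiplicity procedures commonly sit in an analysis plan, and Fig. 2 might mark a primary outcome. This is fair, and the absence of a multiplicity procedure is not the point made here. The primary outcome is core protocol content, and without it the sample-size sentence cannot be interpreted.
- **Sixteen independent tests is an extreme case.** Weight, waist and percent fat are surely correlated, and the HAP also serves to tailor the intervention. This stands, which is why the five-outcome figures are given first. They still exceed 5% about fourfold.
- **The 0.62 may not refer to weight.** It is tempting to assign it to week-24 weight, but nothing in the article supports that.

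**Conclusion.** The concern holds in this limited form. In the visible text the efficacy conclusion has no designated test, so its family-wise error rate is not controlled, although each single test is nominally at 0.05. The size is about 18–23% for the five abstract outcomes and about 37–56% for roughly 16, with correlations between 0.5 and 0. It rests on one interaction test per outcome, equal correlation, and a reading of the results in which any significant outcome could be cited. The stated power is a connected weakness: for a two-sample t-test at 0.62 with 35 per group it is about 0.72.

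**What to change.** Before unblinding, state in the protocol or analysis plan:

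1. One primary efficacy outcome. Body weight fits the stated purpose.
2. One primary test: either the week-24 group difference from the mixed model or the group-by-time test already described.
3. Intent-to-treat as the primary analysis set, with the primary test done once at two-sided 0.05.
4. All other outcomes and the on-treatment analysis as secondary, reported with 95% confidence intervals, with no efficacy claim based on them alone.
5. Which outcome and test 0.62 was actually derived for, from the sponsor's own records, and the power restated for that test at 35 per group.

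The cost is about one paragraph, with no change to data collection. The downside is that secondary scales can no longer support an efficacy claim by themselves, and the restated power may be below 0.80.

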### Outcomes

Outcome measures and timing of administration are listed in Table 2. Clinic visits include routine care, the HAP, and measurement of body weight and body composition (via waist circumference and bioelectrical impedance analysis). Blood samples for measurement of lipids and blood sugar are collected at baseline and week 24. Participants will be required to visit their medical provider at baseline and weeks 6, 12, and 24. During the visits, participants will receive medical supervision that mimics the routine care provided by the clinic. Routine care consists of measuring a patient’s blood pressure, 0_2_ saturation, urinalysis, height, weight, and waist circumference. Medical records will be accessed to collect the participant’s blood sample results. For the POWERS_*for*ID_ intervention clinicians will also measure body composition via bioelectrical impedance analysis and waist circumference. Standard procedures for assessing anthropometrics, such as removal of additional clothing items, measuring from between the lowest rib and iliac crest for waist circumference, will be utilized in line with standardized clinical procedures. The HAP is completed following completion of clinical measures and may be completed with assistance from a caregiver (if applicable) and/or the health coach.

**Table 2 Tab2:** Outcome measures, instruments, and time points

Measures	Instruments	Time point(s)
Adherence	Logs, enrollment metrics, tracking data	Daily
Demographics	Demographics	Baseline
Functional abilities	POWERS_*for*ID_ disability, health and function	Baseline
Body weight	Scale and bioelectrical impedance analysis of body composition	Clinically measured at baseline and weeks 6, 12, and 24
Physical activity behaviors	Physical Activity and Disability Scale; Barriers to Physical Activity and Disability Scale; Exercise Perception Scale; Self-Efficacy Related to Exercise for People with DD Scale	Baseline and weeks 6, 12, and 24
Physical activity	Physical activity points and steps (pedometer)	Daily
Barriers to PA	Barriers to Physical Activity and Disability Scale	Baseline, weekly, 24 weeks
Nutritional behaviors	Block Food Frequency Questionnaire; Fruit and Vegetable Self-Efficacy Scale; Fruits and Vegetables Outcomes Expectancy Scale; Barriers to Fruits and Vegetables Scale	Baseline and weeks 6, 12, and 24
Nutrition	Healthy eating points	Daily
Dietary barriers	POWERS_*for*ID_ dietary barriers	Baseline and weeks 6, 12, and 24

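### The planned adjustment for baseline imbalance names no covariate-by-time term, so on its natural reading it leaves the tested GroupXTime effect practically unadjusted

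*Protocol article*

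**What the plan says.** All the relevant statements are in the Data analysis section of the protocol article.

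- **Adjustment rule:** "Baseline demographics will be entered as time-invariant covariates if baseline group differences are observed".
- **Fixed effects named:** "group (POWERS_*for*ID_ vs. control) as main fixed effects".
- **Random part:** "Intercept will be modeled as random effects".
- **Efficacy criterion:** a more favourable slope in the intervention arm, "which will result in a significant GroupXTime interaction effect".
- **Retention:** the same section expects that "70% of the participants will be retained".

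Table 2 (Outcomes) gives the schedule for weight: "Clinically measured at baseline and weeks 6, 12, and 24". The Intervention section plans 35 participants per group and an effect size of 0.62, and allocates by a simple randomization sequence. No covariate-by-time term is stated anywhere, and none is excluded.

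**The concern.** The section states both a remedy for imbalance and the contrast on which efficacy is judged, and on the ordinary reading the first does not act on the second. A participant-level covariate entered as a main effect explains why some participants are heavier or lighter throughout. It says nothing about why some change faster. The tested effect is a difference in rate of change.

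With 70 participants and simple randomization, a chance imbalance on some demographic is plausible. If that demographic also predicts the rate of weight change, the imbalance stays in the slope difference while the result may be described as adjusted. The main effect also brings essentially no gain in precision on the tested effect. The rule applies to every outcome analysed this way, not only to weight.

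**Working it through.** The plan gives no figure for the adjustment, so there is none to reproduce. Its effect size of 0.62 serves below only as a yardstick. Its power statement raises a separate question that does not bear on this point.

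**Step 1. Complete data, by algebra.** Visits are at weeks 0, 6, 12 and 24 (Table 2).

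- The mean time is (0 + 6 + 12 + 24)/4 = 10.5.
- The deviations are −10.5, −4.5, 1.5 and 13.5. They sum to 0, and their squares sum to 110.25 + 20.25 + 2.25 + 182.25 = 315.
- In a random-intercept model with common visits and linear time, the GroupXTime estimate is Σ(deviation × difference between arm means at that visit)/315.
- A main effect adds the same amount γx to all four of a participant's values. Its contribution is γx × Σ(deviations) = γx × 0 = 0.

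The estimate is therefore the same with or without the covariate, whatever the imbalance.

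**Step 2. Simulation, complete data.** Assumed values, none from the document: covariate SD 1, imbalance 0.5 SD, covariate effect on 24-week change 1.0, random-intercept SD 2, residual SD 1, true GroupXTime effect 0. There were 35 per arm and 150 replicates, fitted by REML. The expected bias is 0.5 × 1.0 = 0.5.

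| Model | Mean GroupXTime, complete data | Mean GroupXTime, 30% attrition |
|---|---|---|
| No covariate | 0.498 | 0.461 |
| Covariate as main effect | 0.498 | 0.462 |
| Covariate and covariate × time | −0.021 | −0.031 |

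With complete data the largest difference between the first two models in any replicate was 5 × 10⁻¹⁵, and their standard errors differed by less than 6 × 10⁻⁶.

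**Step 3. Attrition.** With 30% dropout the main effect moved the estimate by 0.024 on average and 0.088 at most, against a standard error of about 0.41. That is 0.024/0.41 ≈ 6% on average and 0.088/0.41 ≈ 21% at the extreme, with almost no change in the mean bias. Only the interaction with time removed the bias.

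**Step 4. Size on the trial's own scale.** Treat the tested effect as a difference in 24-week change, in SD units. Assume an imbalance of 0.5 SD and a correlation r between covariate and change.

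- Bias = 0.5 × r.
- Standard error = √(2/35) = 0.239.
- Shift s = bias/0.239.
- With the imbalance held fixed, the difference varies only through the part of change that the covariate does not explain. The false-positive rate is therefore about Φ((−1.96 + s)/√(1 − r²)) + Φ((−1.96 − s)/√(1 − r²)).

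| r | Bias (SD) | Share of 0.62 | s | False-positive rate |
|---|---|---|---|---|
| 0.2 | 0.10 | 16% | 0.42 | 6.5% |
| 0.3 | 0.15 | 24% | 0.63 | 8.5% |
| 0.4 | 0.20 | 32% | 0.84 | 11.1% |

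Simulation with the imbalance fixed at 0.5 SD gave 6.4%, 8.4% and 10.9%. With the covariate included in the model of change, the rate was about 5% in each case.

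**Step 5. Averaged over randomization.** When the imbalance is left to chance, the unadjusted test rejects in about 5.0% of trials for each of the three correlations, with mean bias about 0. Among the roughly 5% of trials in which that covariate differs between arms at p < 0.05, the rate is about 7%, 9% and 13–14%. The p < 0.05 cut is an assumption. At 35 per arm it corresponds to a difference of about 1.96 × 0.239 = 0.47 SD.

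**The case against.** The strongest reply is that the article does not say the demographics enter as main effects alone. Time-invariant describes the variable, in contrast to the time-varying outcome named just before it, and not the form of its effect. The list of model terms is plainly condensed: time is not listed, and GroupXTime appears only in the hypothesis. Read with full strictness, the model would lack the very interaction it tests. Exact covariate terms are often left to a full protocol or SAP, and neither is shown.

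Much of this stands. A reader might infer that the plan rules out covariate-by-time terms; the text does not support that. It remains true that the section names an interaction where it wants one and names none for the demographics, so an analyst following the sentence would add the covariates and stop. Silence on a term is harmless when the default works, and here the default does almost nothing to the tested contrast.

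A second reply also stands. A reader might infer from the 6% to 11% that the trial's error rate is inflated. It is not: allocation is random, and the overall rate stays at about 5%. Those figures describe only trials with the assumed imbalance. The article sets no threshold for an observed difference, so the 0.47 SD figure is not the plan's.

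Third, exact invariance needs complete data, and the plan expects 30% attrition. The shift then is small, and its size depends on the values simulated.

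**Conclusion.** The point holds in a conditional form. As written, no covariate-by-time term is stated. If the demographics enter as main effects, the adjustment leaves GroupXTime exactly unchanged with complete common visits, and changed by about 6% of a standard error on average in the 30% attrition simulation. Imbalance on a demographic that predicts change would therefore stay in the tested slope contrast.

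Given a 0.5 SD imbalance and a correlation of 0.2 to 0.4, about 0.10 to 0.20 SD of bias remains, or 16% to 32% of the planned 0.62. Both inputs are assumptions, and a weaker correlation or a smaller imbalance gives less. The statement does not extend to the trial's overall type I error, nor to any claim that the plan forbids the better model. It is worth correcting because the stated remedy, followed literally, would not do its job in the trials that call for it.

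**What to change.** Replace the adjustment sentence in Data analysis with, for example: *Each adjustment covariate enters the model with its main effect and its interaction with time, so that the group difference in slope is adjusted.* Alternatively, estimate the group difference in change at week 24 from a model of change that includes the covariates.

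Beyond the main effect, the cost is one degree of freedom per covariate with linear time; a demographic with several categories, or time fitted as separate visits, costs more. No new data are needed. In the simulation above the interaction slightly lowered the standard error of GroupXTime, from 0.352 to 0.336 with complete data and from 0.409 to 0.395 with attrition. If this model is already intended, stating it costs one sentence.
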